### Methods in analysis to handle protocol non-adherence and any statistical methods to handle missing data {20c}

An intention to treat analysis using linear mixed models will be used to compare outcomes between the intervention and control arm and account for the correlation within-subject over time, while adjusting for differences in participant characteristics at baseline where appropriate. A sensitivity analysis, via multiple imputation, will be used to explore whether adherence to the intervention influences the effect of the intervention on the primary outcome.

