### Criteria for discontinuing or modifying allocated interventions {11b}

CGA is a dynamic process and may change depending on the patient's presentation. Participation in the study is voluntary. Participants will be free to withdraw consent and leave the study at any time without giving a reason and without affecting their care. Should a patient withdraw consent to participate in the study, we will seek clarification on whether withdrawal is from a particular element of the study, for example, participation in the CGA, questionnaire completion or access to healthcare records. Previously collected anonymised data will still be used in the analyses. In cases where participants do not respond to follow-up assessments, outcome data that do not involve participant contact (e.g. data from hospital database) will continue to be collected in these cases.

No formal interim analyses are planned for the primary or secondary outcomes. A single final analysis is planned after the study is closed to recruitment and follow-up and when the full database has been screened, cleaned and prepared for analysis.

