### Sample size {14}

We estimated the sample size based on the primary outcome (ED length of stay) using G*Power version 3.1. Using data from the Patient Experience Time (PET) database employed in the ED at UHL (unpublished data), the average ED length of stay for patients aged 75 and older for the 2019 yearly period was 18.63 h (standard deviation 19.91 h). Estimating a 50% decrease in ED length of stay in the intervention group (mean 9.31 h), and with a 20% attrition rate to follow-up, a sample size of 236 patients (118 in each group) will be required to achieve 90% power with two-tailed tests at an alpha level of 0.05.

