## Statistical methods

### Statistical methods for primary and secondary outcomes {20a}

Appropriate descriptive statistics will be used to describe the baseline characteristics of study participants. These will include proportions, percentages, ranges, means and standard deviations and medians and interquartile ranges (where data are not normally distributed). We will analyse differences across the two groups for all continuous outcomes (ED length of stay, etc.) by using independent samples *t* tests with 95% confidence intervals. The non-parametric equivalent, the Mann-Whitney test, will be used for skewed data.

Incidence of ED return, unplanned hospital admission, nursing home admission and healthcare utilisation will be explored using crude and adjusted risk ratios with associated 95% confidence intervals using logistic regression. Unit costs will also be applied to resource use data. The total costs of health and social care input will be compared between groups with complete resource utilisation data, using non-parametric bootstrapping (it is anticipated that the data will be highly skewed in terms of distribution). A 5% level of statistical significance will be used throughout the analyses.

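### Multiple imputation is attached to adherence on a near-complete primary outcome, while the cost comparison drops participants with incomplete resource-use data whose hospital use is still being collected

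*Protocol article*

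**What the plan says.** Section {20c} of the Protocol article is headed as covering both non-adherence and missing data. It makes two commitments. The first is a model: "An intention to treat analysis using linear mixed models will be used to compare outcomes between the intervention and control arm", allowing for within-subject correlation over time and, where appropriate, baseline differences. The second is the only use of imputation in the document: "A sensitivity analysis, via multiple imputation, will be used to explore whether adherence to the intervention influences the effect". That sentence concerns the primary outcome alone. No adherence variable, imputed variable or estimand is attached to it.

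Section {20a} gives t tests, or Mann-Whitney tests if the data are skewed, for every continuous outcome, and logistic regression for the event and utilisation outcomes. For costs it says: "The total costs of health and social care input will be compared between groups with complete resource utilisation data", by non-parametric bootstrap.

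Three other places bear on this:
- Sample size {14} plans "with a 20% attrition rate to follow-up".
- Section {11b} says that for those who do not respond, "outcome data that do not involve participant contact (e.g. data from hospital database) will continue to be collected in these cases".
- Outcomes {12} defines the primary outcome as the time from arrival to leaving the ED or AMAU, and takes GP, public health nurse and allied health use from the 30-day telephone call.

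**The concern.** Multiple imputation replaces missing values under an assumed model. It does not by itself say how receiving the geriatric assessment, as opposed to being allocated to it, alters length of stay. Followed literally, the plan would impute a variable that is almost fully observed, and the result could be reported as an adherence analysis when it is not one. The question matters here. Assessment may be by one or more team members ({11a}), and some controls are seen by OPTIMEND, which delivers parts of the same assessment ({20b}).

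The missing data will arise elsewhere, in the telephone follow-up. The one explicit rule that touches them is the restriction of the cost comparison to complete resource-use data. Cost-effectiveness is part of the trial's overall aim. The rule removes randomised participants from that comparison because of something that happens after randomisation, and discards hospital-use data the trial already holds for them.

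**Working it through.** **1. The plan's own figure.** Inputs from {14}: means 18.63 h and 9.31 h (difference 9.32 h), SD 19.91 h, two-sided alpha 0.05, power 90%, attrition 20%, total 236 (118 per arm).
- Normal approximation: n = 2 × (1.960 + 1.282)² × (19.91 / 9.32)² = 95.9, so 96 per arm. Dividing by 0.8 gives 120 per arm (240 in total); multiplying by 1.2 gives 116 per arm (232).
- Exact t test: 97 per arm. Multiplying by 1.2 gives 117 per arm (234); dividing by 0.8 gives 122 per arm (244).

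The stated 236 lies within 3% of 240, 232 and 234, and just outside that of 244. It is reproduced to ordinary tolerance and is not in dispute. It is used below only for scale.

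**2. Where data can go missing.**
- Primary outcome ({12}): a recorded time that closes when the participant leaves the ED or AMAU. Later loss to follow-up cannot remove it.
- Hospital-recorded outcomes: collection continues for non-responders ({11b}).
- Barthel and EQ-5D at 30 days, and GP, public health nurse and allied health use: these need the telephone call ({12}). Participants who drop out after the intervention are not telephoned ({26a}).

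**3. How many could leave the cost comparison.** Under Economic evaluation the cost items include GP and public health nurse visits, so a telephone non-responder lacks complete resource use. Taking the 20% as telephone non-response (an assumption, because {14} ties it to no outcome or visit): 0.20 × 236 = 47.2, about 47 people, leaving 188.8, about 94 per arm. At 10% the loss would be about 24 and at 30% about 71.

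**4. What that can do to costs.** In arm a, let m_a be the proportion missing, R_a the mean cost of responders and N_a that of non-responders. The true mean is (1 − m_a)R_a + m_a N_a, and the complete-case mean is R_a.
- Bias within an arm: −m_a(N_a − R_a).
- Bias in incremental cost (intervention minus control): −[m₁(N₁ − R₁) − m₀(N₀ − R₀)].

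The documents give neither N − R nor m by arm, so the second quantity cannot be computed. For the first, with m = 0.2 and an assumed cost ratio g = N/R, the relative bias is 1/(0.8 + 0.2g) − 1: −4.8% at g = 1.25, −9.1% at g = 1.5 and −16.7% at g = 2. These are biases in one arm's mean. If m and g are the same in both arms, the difference shrinks by that same factor and a true difference of zero stays zero. The sign or the null can be distorted only if m or g differs between arms.

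**5. What an adherence analysis needs.** With randomisation as instrument, the complier average causal effect is ITT / (p₁ − p₀), where p₁ and p₀ are the proportions receiving the defined treatment in each arm. Its inputs are allocation, length of stay and receipt. All are recorded; {18a} says details of the SOLAR assessment are charted and collected. No step calls for imputation.

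**6. {20a} against {20c}.** A t test on the 30-day Barthel drops anyone without a 30-day value. A likelihood-based mixed model over baseline and 30 days keeps those with a baseline value and is valid under missing at random. The two sections prescribe different analyses, with different missing-data behaviour, for the same outcome.

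**The case against.** The strongest reply is that {20c} does contain a sound approach to missing follow-up. The mixed model precedes the imputation sentence, and Barthel and EQ-5D are measured at baseline ({18a}) and at 30 days, so it can be applied to them. A reader might infer that all telephone outcomes get a complete-case analysis. The document does not say so: that handling is only implied by the tests in {20a}, and {20c} points the other way. What stands is the conflict, and the fact that a linear model over time does not serve nursing home admission, 30-day community use or total cost.

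Second, imputation can serve an adherence question if outcomes after non-adherence are set to missing and imputed for a hypothetical estimand. That is correct, so it would be wrong to say imputation can never address adherence. Nothing in {20c} states such an estimand. An unseen analysis plan may supply the imputation model and similar detail, and none of that is held against the protocol here. The point is the pairing the protocol does state.

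Third, a reader might infer that those dropped are the sickest and the most costly. This is not established. Section {18b} provides several telephone numbers, help from next of kin and reference to hospital systems, and hospital use continues to be captured. Community use by telephone is described only at 30 days, so 6-month non-response need not affect it. These measures reduce the loss. They do not change the rule that an incomplete record leaves the cost comparison.

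Finally, a complier effect larger than the ITT effect (1.11 to 1.43 times it for an assumed 90% to 70% receipt with no control receipt) is not an error in the plan. ITT remains the right main analysis.

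**Conclusion.** The concern holds in limited form and should be corrected before the data are analysed. The imputation-based adherence analysis does not answer its question as stated. The complete-case cost rule excludes telephone non-responders, about 47 of 236 if the planned 20% attrition falls on the telephone calls, while their hospital use is still collected. Sections {20a} and {20c} conflict on follow-up outcomes.

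The direction and size of any bias in incremental cost are unknown. Bias that could create or reverse a difference requires non-response to be related to cost and to differ by arm. Differential non-response is possible, since participants are not blinded ({17a}) and only one arm meets the team, but the documents give no evidence of it. It would go too far to infer that the cost-effectiveness result is invalid or that the trial's main conclusion is at risk: the sample size and the primary intention-to-treat comparison of length of stay are untouched.

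**What to change.** 1. Replace the imputation-based adherence sentence with an analysis that targets adherence, for example a complier average causal effect on length of stay by two-stage least squares, with randomisation as instrument and receipt of the SOLAR assessment before leaving the ED or AMAU as the adherence variable. State the exclusion restriction (allocation affects length of stay only through receipt), and state how controls seen by OPTIMEND are classified, since p₀ depends on it.
2. Apply multiple imputation, by arm, to the cost and QALY analysis and to telephone-only outcomes, using baseline Barthel, baseline EQ-5D and hospital-record utilisation as predictors. Treat deaths as observed, not as missing. Keep complete-case costs as the sensitivity analysis.
3. Reconcile {20a} with {20c}: name one main analysis for each follow-up outcome, and say where the mixed model applies and where the t test, Mann-Whitney test or logistic regression does.

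No new data collection is needed. The cost is protocol or analysis-plan wording, some extra programming (including combining imputation with the bootstrap), and reliance on missing at random given the listed predictors. The complete-case result will give a partial check on that assumption.

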### Plans to give access to the full protocol, participant level-data and statistical code {31c}

The anonymised dataset will be stored in a public data repository and supplementary data will be available on request.

## Oversight and monitoring

### Composition of the coordinating centre and trial steering committee {5d}

Given the nature of this trial, The Trial Steering Committee (TSC) will comprise of the PI, key co-applicants, SOLAR team and other key external members of staff involved in the study. Specifically, the TSC will be responsible for: protocol development; obtaining ethical approval; clinical set-up; on-going management; promotion of the study; interpretation and publishing of the results. The TSC will provide overall supervision of the study; in particular monitor study progress, and provide public, clinical, and professional advice, with pre-agreed terms of reference.

### Composition of the data monitoring committee, its role and reporting structure {21a}

For a study of this nature, a separate data monitoring committee is not required. The TSC will serve this function.

### Adverse event reporting and harms {22}

No physical, psychosocial, or financial harm is expected to result from taking part in the study. Participants may decide to withdraw from the study at any time, in which case they have the right to do so without any adverse impact on their current or future care.

Any unexpected adverse events will be documented by the research nurse at 30 days and 6 months and the GP will be notified. Participants will be advised to go to the ED if an adverse event requires urgent assessment.

### Frequency and plans for auditing trial conduct {23}

Trial conduct will be monitored each week by the PI and SOLAR team. A formal meeting will take place in which the team (PI and lead investigator) will discuss the intervention and ensure that there is consistency in the conduct of the intervention. Any deviations from the protocol will be discussed and feedback given to the wider SOLAR team. An Independent research nurse will oversee the data management procedures. The SOLAR trial is also subject to the standard operating procedures of our local clinical research unit (Health Research Institute).

### Plans for communicating important protocol amendments to relevant parties (e.g. trial participants, ethical committees) {25}

All protocol amendments will be notified to the Research Ethics Committee. Any deviations from the published protocol will be documented on the trial registration open platform and in the final manuscript detailing the trial outcome.

### Dissemination plans {31a}

The study has been registered with an authorised registry (ClinicalTrials.gov), according to International Committee of Medical Journal Editors (ICMJE) guidelines, prior to the start of recruitment. Uniform requirements for authorship for manuscripts submitted to medical journals will guide authorship decisions.

The TSC will agree on a publication plan and must be consulted prior to release or publication of any study data. Individual collaborators must not publish data concerning their participants which is directly relevant to the questions posed in the study until the main results of the study have been published. Local collaborators may not have access to study data until after publication of the main study results. A lay summary of the findings will be presented in collaboration with the Patient and Public Involvement stakeholder group of older people at the Ageing Research Centre, University of Limerick.

## Discussion

There have been many interventions introduced in the ED and AMAU which aim to improve outcomes for older frail adults. The interventions and the outcomes assessed have been heterogenous. Preston et al. have described four clusters of interventions which have been highlighted as potentially effective: discharge intervention, staff focused, population focused and intervention component [17]. Overall, none of these systematic reviews have shown a clear benefit of CGA in the ED. Hughes et al. showed that strategies in the ED with multiple interventions may be more beneficial than single interventions alone, however, these multidomain interventions are more difficult and laborious to perform [18]. The SOLAR intervention will be multidisciplinary and interdisciplinary in nature under the governance of a consultant geriatrician and/or ED consultant.

## Trial status

Recruitment commenced on November 9th, 2020, and is due to finish in June 2021. Follow-up will be completed in December 2021.

## Data Availability

Individual data will be available in a data repository once the study analysis has been completed.

## Abbreviations

ED: Emergency department
CGA: Comprehensive geriatric assessment
ISAR: Identification of Seniors At Risk
AMAU: Acute Medical Assessment Unit
HSE: Health Service Executive
PPI: Patient and Public Involvement
UHL: University Hospital Limerick
GP: General Practitioner
PET: Patient Experience Times
QALYs: Quality Adjusted Life Years
PI: Primary Investigator
TSC: Trial Steering Committee
